#### Secondary outcome analyses

Statistical analysis of change in time spent within target range will be performed according to the same schemata used for the primary outcome. Other secondary outcome variables will be compared descriptively by study groups for each scheduled visit and for changes between visits. Continuous variables, including scores from the questionnaires will be summarised using N, mean, SD, median, lower and upper quartile, minimum and maximum; categorical variables will be summarised using counts and percentages of participants in each category. Two-sample t-tests in the case of continuous variables and chi-square tests in the case of categorical variables will be performed for group comparisons. Graphical techniques will be used to display changes over time, if appropriate. Pearson correlation coefficients will be computed between all variables of interest.

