#### Secondary endpoints

*Time within Target Range:* CGM data (from 50-60% of participants) will be used to assess the change in time spent within the target bG range of 72–180 mg/dl from baseline to study end. CGM data will be collected at Visits 2 (week minus 1), 7 (week 12), and 9 (week 24).

*Other Glycaemic Measures:* Glucose data from 3-day glycaemic profiles, derived from uploaded SMBG and CGM data (when applicable) will be used to assess: 1) frequency of hypoglycaemia (within 50–72 mg/dl) and severe hypoglycaemia (<50 mg/dl with associated symptoms), overall, and by defined time blocks (12:00 a.m. to 5:00 a.m., 5:00 a.m. to 10:30 a.m., 10:30 a.m. to 4:30 p.m., 4:30 p.m. to 12:00 a.m.); 2) total number of SMBG tests and average number of SMBG tests per day and by the defined time blocks; 3) percentage of all values, preprandial values (60–0 minutes prior to meal) and postprandial values (60–180minutes after start of meal) within defined bG ranges (<50 mg/dl, 50–72 mg/dl, 72–180 mg/dl, 180–300 mg/dl, #62;300 mg/dl); 4) mean bG across the 3-day profiles and for each of the 7 time points; 5) standard deviation (SD) and coefficient of variation across the 3-day profiles; 6) Mean and SD differences between preprandial and postprandial bG values over each meal in the 3-day profiles; 7) mean amplitude of glycaemic excursions (MAGE), low bG index (LBGI), high bG index (HBGI), bG risk index (BGRI) and risk for hypoglycaemia and hyperglycaemia across the 3-day profiles. The 3-day glycaemic profile data will be collected at Visits 2 (week minus 2), 5 (week 4), 7 (week 12) and 9 (week 24).

*Automated Bolus Advisor Use and Participants’ Adjustments (EXP Group):* The frequency of participants’ bolus advisor use and subsequent adjustments based on proposed bolus amounts will be derived from data uploads of the automated bolus advisor device. Analyses will include: average number of times per day participants sought advice for mealtime and correction bolus calculation; average number of times per day participants accepted the automated bolus advisor advice; average number of insulin doses adjusted up or down per day; average number of times participants accepted the automated bolus advisor responses and adjusted boluses within specific time periods (a.m., p.m., after 10 p.m.); and differences between the average number of adjusted mealtime boluses and adjusted correction boluses.

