#### Primary outcome analysis

Anticipated attrition of 20% will yield a sample size of 180 (90 per study group), which will provide #62;80% power to detect a mean difference of 0.5% in change in HbA1c, with SD of 0.9%. The absolute and relative change in HbA1c from baseline to study end for the CNL and EXP groups will compared using the two-sample *t*-test for the pooled ITT population. These tests will be performed at the one-sided 5% level of significance for rejecting the null hypothesis of no difference or a difference in favor of the CNL group. An analysis of covariance with the binary covariables (study group, sex and diabetes type) and the continuous baseline covariables (HbA1c, age and CHO counting assessment score) will be performed for the absolute and relative HbA1c change. Additional separate analyses of (co)variance will be performed using two explanatory variables (study group and one adjusting covariable) for the above mentioned covariables and other baseline covariables (e.g., country, center, time since diabetes diagnosis, existing diabetes related diseases, time since MDI start, bG measures from SMBG at baseline, frequencies of hypoglycaemia at baseline, laboratory parameters and, summary scores from psychosocial questionnaires) for the pooled groups. The one-sided 95% confidence intervals of the HbA1c change for CNL and EXP groups and the difference between the groups will also be calculated for the pooled groups.

Summary statistics (N, mean, median, SD, lower and upper quartile, minimum and maximum) will be provided for the observed HbA1c values by study group for each applicable scheduled visit (Visits 1, 6 and 9). Graphical techniques will be used to display the HbA1c change over time.

Pearson correlation coefficients will be computed for the HbA1c values at Visits 1, 6, and 9 and the absolute and relative HbA1c changes from baseline to study end vs. demographic and clinical variables; bG measures from SMBG and CGM scores for each collection visit, other laboratory parameters, frequencies of hypoglycaemia, CHO scores; and summary scores from psychosocial questionnaires. For all of these covariables, the correlation coefficients for their changes from baseline vs. the HbA1c parameters will be computed, too. Additionally, the correlation coefficients for the HbA1c parameters vs. bolus advisor parameters will be computed for the EXP group.

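### Time in range inherits formal testing of relative change from the HbA1c scheme, alongside absolute change and with neither named as decisive; the scale suits HbA1c but not a percentage that can approach zero

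*Protocol article*

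**What the plan says.** The Secondary endpoints section defines the outcome: CGM data will be used to "assess the change in time spent within the target bG range of 72–180 mg/dl from baseline to study end". The data come from a subset: "CGM data (from 50-60% of participants) will be used".

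Secondary outcome analyses then sets the method by reference: "Statistical analysis of change in time spent within target range will be performed according to the same schemata used for the primary outcome". The scheme it points to is in Primary outcome analysis:

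- Two-sample t-tests compare "The absolute and relative change in HbA1c from baseline to study end for the CNL and EXP groups".
- The level is fixed: "These tests will be performed at the one-sided 5% level of significance".
- An ANCOVA with study group, sex and diabetes type, plus "the continuous baseline covariables (HbA1c, age and CHO counting assessment score) will be performed for the absolute and relative HbA1c change".

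The article does not say which of the two scales decides, and gives no rule for a zero or very low baseline time in range. Time in range is listed first among the secondary outcomes and is the only one given the primary outcome's scheme. The others are to be compared descriptively, with simple t-tests or chi-square tests.

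**The concern.** On its plain reading, the reference carries relative change over to time in range as a formally tested quantity. This is a stated rule, not a detail left open.

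Relative change divides by the baseline value. For HbA1c, entry above 7.5% keeps every divisor at about that value or higher, so relative change is close to a rescaling of absolute change. Time in range has no such floor. The same gain in percentage points becomes a very different relative change depending on where the participant started, and a few low baselines can dominate the mean and SD of that variable.

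Two things are at stake. The relative-change test has less power, in an outcome measured in only about half the participants. And the two co-listed tests can give different answers, with nothing in the plan to say which counts.

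**Working it through.** **The plan's own figures.** No power figure is given for time in range. For HbA1c with 90 per group, difference 0.5, SD 0.9 and one-sided 5%, the standard error is 0.9 × √(2/90) = 0.134. Then 0.5/0.134 − 1.645 ≈ 2.08, which is a power of 98.1%. The stated figure of more than 80% is therefore true as a lower bound. The recruitment figure also reproduces: 90/0.8 = 112.5, rounded up to 113 per group.

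**Size of the CGM subset.** 50-60% of 90 completers per arm is 0.5 × 90 = 45 to 0.6 × 90 = 54.

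**Algebra.** Relative change is (F − B)/B, with B the baseline and F the follow-up value. A gain of 10 points is:

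| Baseline time in range | Relative change |
|---|---|
| 60% | +17% |
| 40% | +25% |
| 10% | +100% |
| 5% | +200% |
| 2% | +500% |
| 0% | undefined |

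By contrast, under an assumed baseline HbA1c of mean 8.9 and SD 1.1, absolute and relative HbA1c change correlate at 0.99 and the relative change has almost no skew.

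**Assumptions for the simulation (none is in the article).** Beta-distributed time in range with the means and SDs shown, baseline to follow-up correlation 0.6, a true benefit of 8 points or none, and one-sided 5% two-sample t-tests.

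*45 and 54 per arm, no change in the control arm:*

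| Baseline mean/SD | Power, absolute change (45; 54) | Power, relative change (45; 54) | Control-arm mean relative change with no true change | Participants with baseline below 5% |
|---|---|---|---|---|
| 55/15 | 88%; 93% | 76%; 83% | +4% | about 0% |
| 45/15 | 88%; 93% | 75%; 82% | +6% | about 0% |
| 40/18 | 76%; 81% | 58%; 62% | +14% | 0.6% |
| 30/15 | 87%; 92% | 70%; 76% | +17% | 1.6% |
| 25/15 | 87%; 92% | 65%; 71% | +28% | 5.3% |

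The median relative change with no true change is about 0 throughout, so the positive means in the fourth column are produced by skew (1.5 at 55/15, about 5-6 at 40/18, above 12 at 25/15).

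*50 per arm, both arms rising by 3 points and the bolus advisor arm by a further 8:*

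| Baseline mean/SD | Relative-change t-test | Absolute-change t-test | ANCOVA with baseline time in range |
|---|---|---|---|
| 50/15 | 79% | 91% | 95% |
| 45/17 | 64% | 84% | 91% |
| 40/18 | 53% | 77% | 85% |

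**Varying the correlation.** Over correlations of 0.4-0.75 and baselines from 55/15 to 40/18, with 50 per arm and 8 points, the relative-change t-test has about 5-28 points less power than the absolute-change t-test. One is significant and the other not in about 6-31% of trials. The low ends belong to high correlation and high baseline; the high ends to low correlation and the 40/18 baseline.

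**Type I error.** With no true effect, each test taken singly rejects near the nominal level: 4.6-5.6% for absolute and 4.2-5.2% for relative change.

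**The case against.** The other side has several good points.

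- **Near-zero baselines are not shown.** A reader might infer that this trial enrols people whose time in range is close to zero. The article does not support that. It defines participants by HbA1c above 7.5% and gives no baseline time in range. In the scenarios with means of 40-55%, at most 0.6% of participants start below 5%. This stands. However, the power loss does not need near-zero baselines: it is already 88 − 76 = 12 points at 55/15 with 45 per arm.
- **No false positives.** A reader might infer that outliers could manufacture a positive result. Each test keeps its level, so they do not. The low baselines cost power and distort the mean.
- **A real benefit is not lost.** Absolute change is tested under the same scheme, with 76-93% power in the first table. This limits the harm. What remains is that the plan does not say which scale counts when they differ.
- **The baseline covariate is an ambiguity.** A reader might infer that the ANCOVA leaves out baseline time in range, because the list names HbA1c. That is the literal reading only; applying the same scheme to another outcome can equally mean using that outcome's own baseline. If so, the ANCOVA power above is close to what is already planned and is not a gain from the fix.
- **This is a condensed article.** A fuller analysis plan, not shown, might narrow the reference. That is possible, but the article does state the rule, and as stated it includes relative change.

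**Conclusion.** The point holds as a choice of scale for one secondary outcome. The cross-reference makes relative change in time in range a formal one-sided test beside absolute change, without ranking them, on a variable for which division by baseline works poorly.

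The cost is about 5-28 points of power on the relative scale and differing verdicts in about 6-31% of trials. These figures rest wholly on assumed values: baseline mean 40-55% with SD 15-18, correlation 0.4-0.75, 50 per arm and a true 8-point benefit. The direction is the same in every scenario examined; the size is not known for this trial.

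The HbA1c analysis and the validity of the absolute-change test are not in question. Correcting or demoting relative change for HbA1c alone would not settle this outcome unless the Secondary outcome analyses sentence is changed too.

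**What to change.** In Secondary outcome analyses, replace the bare reference for time in range with a sentence to this effect:

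> The inferential analysis of time in range is the absolute change from baseline to study end, in percentage points, by the ANCOVA of the primary outcome, with baseline time in range in place of (or added to) baseline HbA1c and with study group, sex, diabetes type, age and CHO counting score retained; relative change is summarised descriptively only.

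Deleting relative change for this outcome would serve equally well. Keeping the other covariates, including the CHO counting score, leaves the prespecified model otherwise intact. Naming baseline time in range removes the ambiguity about which baseline is meant.

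The cost is one sentence and at least one fewer formal test. No further data or participants are needed.

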*Participant Adherence/Use of Rule Sets:* Changes in participants’ therapy adherence to and use of rule sets in EXP participants will be derived from downloaded data obtained from automated bolus advisor devices. Adherence in CNL participants will be derived from documented therapy parameters and participants’ diaries, which are included in 3-day glycaemic profile forms. These assessments will be used to determine if participants’ adherence/use of rule sets correlates with improvement in glycaemic control. Analyses will include: average number of correctly and incorrectly used insulin-to-carbohydrate (I:CHO) rules per day for CHO intake; average number of correctly and incorrectly used insulin sensitivity factor (ISF) rules per day for bG adjustment; and number of changed I:CHO and ISF parameters compared to therapy parameters at study start (Visit 3). Data will be collected at Visits 2 (week minus 2), 5 (week 4), 7 (week 12) and 9 (week 24).

*CHO Counting:* Changes from baseline in participants’ ability to accurately count CHO will be assessed using the DAFNE plate assessment scores from Visit 1 (week minus 2) and 9 (week 24). This assessment will be used to determine if participants’ CHO counting skills correlates with improvement in glycaemic control.

*Psychosocial Outcomes*: Psychosocial outcomes including treatment satisfaction, social functioning and factors important to quality of life will be assessed using the participant questionnaire, which incorporates questions from validated psychometric instruments, as well as commonly used survey questions, to assess depression, diabetes-specific distress, diabetes self-efficacy, treatment satisfaction, health outcomes and fear of hypoglycaemia. Participant questionnaire items include: Patient Health Questionnaire depression scale (PHQ-8) [25]; Problem Area in Diabetes (PAID) [26]; Hypoglycaemia Fear Scale (HFS –II) [11];Diabetes Treatment Satisfaction Questionnaire (DTSQs, [baseline] and DTSQc [change]) [27];Gold Scale [28];and EuroQol-5 Dimensions-5 Levels measure (EQ-5D-5L) [29] (Table 2). The questionnaires will be administered at Visits 1 (week minus 2), 7 (week 12) and 9 (week 24); however, the DTSQs and DTSQc portions will be administered only at Visits 1 and 9.

**Table 2 T2:** Participant Questionnaire components

**Instrument**	**Description**	**Scoring**

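### Most continuous secondary outcomes have a baseline but are tested by unadjusted two-sample t-tests; ANCOVA would be more precise, and hypoglycaemia should be analysed per reading in case reading numbers differ between arms

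*Protocol article*

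**What the plan says.** Under Secondary outcome analyses, the Protocol article treats one outcome apart: "Statistical analysis of change in time spent within target range will be performed according to the same schemata used for the primary outcome". Those schemata (Primary outcome analysis) comprise a two-sample t-test and a covariate model: "An analysis of covariance with the binary covariables (study group, sex and diabetes type) and the continuous baseline covariables (HbA1c, age and CHO counting assessment".

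All other secondary outcomes follow a simpler rule: "Other secondary outcome variables will be compared descriptively by study groups for each scheduled visit and for changes between visits". The same paragraph then fixes the tests: "Two-sample t-tests in the case of continuous variables and chi-square tests in the case of categorical variables will be performed for group comparisons". No baseline covariate is named.

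Baselines are collected for most of these outcomes (Secondary endpoints). On the questionnaires: "The questionnaires will be administered at Visits 1 (week minus 2), 7 (week 12) and 9 (week 24"), with the two DTSQ forms limited to Visits 1 and 9. The 3-day glycaemic profiles start at Visit 2, and the DAFNE plate score is taken at Visits 1 and 9.

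Hypoglycaemia is listed as "frequency of hypoglycaemia (within 50–72 mg/dl) and severe hypoglycaemia (<50 mg/dl with associated symptoms), overall, and by defined time blocks", drawn from the 3-day profiles using SMBG data and, where available, CGM data. No unit or denominator is given. The same list contains "total number of SMBG tests and average number of SMBG tests per day and by the defined time blocks", and also the percentage of readings in defined ranges, including the two low ranges, and LBGI.

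**The concern.** The plan collects a baseline, accepts covariate adjustment for HbA1c and time in range, and then leaves it out for most other continuous outcomes. Primary outcome analysis even names baseline hypoglycaemia frequency and psychosocial summary scores as covariables, but only in models for HbA1c, not for their own follow-up values.

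The result is two tests per outcome. The visit-value test ignores the baseline. The change test subtracts all of it, which is more than the correlation warrants whenever that correlation is below 1. The two can lead to different conclusions, and the article does not say which leads. Hypoglycaemia, glucose variability and psychosocial outcomes are part of the hypothesis in the Background. The sample size rests on HbA1c alone, so precision for these outcomes is whatever the analysis can extract.

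Hypoglycaemia frequency adds a separate question. If it were analysed as a count, it would depend on how many readings each participant supplies, and the article gives no exposure term.

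**Working it through.** **The plan's own figure.** The only power statement concerns HbA1c: more than 80% with 90 completers per arm, difference 0.5, SD 0.9, one-sided 5%. Check: 0.5 / (0.9 × √(2/90)) = 3.73; 3.73 − 1.645 = 2.08; power 98.1%. The stated figure holds as a lower bound. No figure is given for the secondary outcomes, and nothing below depends on this one.

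**Precision.** Let r be the baseline-to-follow-up correlation, with equal SD at both times. The article gives no r, so 0.3 to 0.7 is an assumption. Relative variance of the group difference:
- t-test on visit value: 1
- t-test on change: 2(1 − r)
- ANCOVA: 1 − r²

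The ratio of ANCOVA to the change test is (1 − r²) / [2(1 − r)] = (1 + r)/2.

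| r | Change test | ANCOVA | ANCOVA ÷ visit value | ANCOVA ÷ change |
|---|---|---|---|---|
| 0.3 | 1.40 | 0.91 | 0.91 | 0.65 |
| 0.5 | 1.00 | 0.75 | 0.75 | 0.75 |
| 0.7 | 0.60 | 0.51 | 0.51 | 0.85 |

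Inverted, the t-tests carry 10% to 96% more variance than ANCOVA on visit values and 18% to 54% more on changes. At r = 0.5, ANCOVA with 90 per arm matches either t-test with 90 / 0.75 = 120 per arm.

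As power, take an assumed difference of 0.4 SD, 90 per arm, two-sided 5% (effect and sidedness are assumptions). For the visit-value test, 0.4 / √(2/90) = 2.68; 2.68 − 1.96 = 0.72; power 77%. The other tests divide 2.68 by the square root of their relative variance:

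| r | Visit value | Change | ANCOVA |
|---|---|---|---|
| 0.3 | 77% | 62% | 80% |
| 0.5 | 77% | 77% | 87% |
| 0.7 | 77% | 93% | 96% |

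Neither t-test is consistently the better one: the change test is worse below r = 0.5 and better above it. ANCOVA is at least as good as both throughout.

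**Where ANCOVA cannot apply.** Bolus advisor use and adjustments exist only in EXP and only from Visit 3, when the device is issued. DTSQc is itself a change score (items from −3 to 3). Changed I:CHO and ISF parameters are counted from Visit 3.

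**Hypoglycaemia.** The profile is 7 points on 3 days, so 21 planned readings in each arm. The completeness rule of at least 80% (0.8 × 21 = 16.8, so 17 readings) governs only the PP population, while efficacy and safety are analysed on ITT. Simulation: 90 per arm, identical risk per reading in both arms, individual risk beta-distributed with mean 5% to 12% (beta parameters summing to 15), 10,000 runs, two-sided 5%. All of these except the 90 are assumptions.

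| Readings, EXP v CNL | Ratio of mean counts | False positives, t-test on counts | Same test on share of readings |
|---|---|---|---|
| 21 v 21 | 1.00 | about 5% | about 5% |
| 21 v 19 | 1.11 | 8% to 12% | about 5% |
| 21 v 17 | 1.24 | 16% to 33% | about 5% |

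The bias is nil with equal readings and grows with the imbalance. A per-reading share removes it.

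**The case against.** **The t-tests are not wrong.** With 1:1 randomisation, comparisons of visit values and of changes both estimate the group difference without bias and at the correct size. A reader might infer that the secondary results would be invalid, or that baseline is ignored altogether. Neither follows: the change test does use baseline, only less efficiently. This stands, and it confines the first part to precision.

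**The comparisons are called descriptive, and no secondary power target exists.** The stated comparison is "compared descriptively by study groups for each scheduled visit and for changes between visits". That lowers the stakes, but the same paragraph goes on to prescribe tests, so the choice of test is part of the plan.

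**The gain depends on an unknown r.** At r = 0.3, ANCOVA adds about 3 points of power over the visit-value test; at r = 0.7, about 3 over the change test. This stands. The equivalent of one third more patients belongs to r = 0.5 only.

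**The hypoglycaemia bias is not established.** A reader might infer that more testing in EXP will show up as more hypoglycaemia, because the advisor works from a current glucose value. The article does not support that as stated. Events come from a fixed 21-point profile, frequency is not said to be a raw count, and percentage in range and LBGI do not grow mechanically with the number of tests. The denominator may also be defined in a fuller document not shown, so its absence from an article is no finding in itself. What remains is conditional: incomplete profiles in ITT, extra uploaded readings, or mixed CGM and SMBG data could make readings unequal.

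**Conclusion.** The concern holds as an avoidable loss of precision, not as a validity error. It covers continuous secondary outcomes that have a baseline: questionnaire scores other than DTSQc, 3-day-profile glucose measures and the CHO counting score. Time in target range is already handled. It would be an overstatement to say that every secondary outcome has a baseline: bolus advisor use, DTSQc and parameter changes from Visit 3 do not.

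Size: ANCOVA variance is 0.91 to 0.51 of the visit-value test's and 0.65 to 0.85 of the change test's for r from 0.3 to 0.7, and 25% below both at r = 0.5. This rests on the assumed r and on equal SDs at baseline and follow-up.

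The hypoglycaemia point is secondary and conditional. If readings per patient differ between arms, a t-test on counts is biased: at 21 v 17 readings, a 24% apparent excess and 16% to 33% false positives under the assumed risks. If both arms complete the 21-reading profile, there is no such bias.

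**What to change.** In Secondary outcome analyses, for between-group comparisons of continuous outcomes that have a baseline, replace the two-sample t-tests by ANCOVA of the follow-up value on study group, the outcome's own baseline and diabetes type. Report the adjusted difference with its confidence interval. Keep the unadjusted visit and change summaries as descriptive tables. State that bolus advisor use, DTSQc and parameter changes from Visit 3 are excluded from this rule.

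For hypoglycaemia, analyse per reading: either the share of readings, or a negative binomial model with log(number of readings) as offset. An offset of log(days) would not serve, because within a fixed 3-day window it is essentially constant and leaves unequal reading numbers uncorrected. Analyse CGM and SMBG sources separately.

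The cost is wording and a little programming, with no new data. Participants without a baseline value need a simple baseline imputation or drop out of that outcome's model; the change test already loses them.
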